### Data collection

At baseline and 3, 6, 9 and 12 months, respectively, from the participant’s inclusion in the study, an email containing a link to an online questionnaire will be sent to the participants. All collected data will be self-reports, including a 30 s chair stand self-test (30CST). In the absence of completed questionnaires, a reminding email will be sent out after 1 week. If further absence, another email will be sent after an additional week. This reminder will also include a question if they want to withdraw from the study. Data registered in the exercise diary of the application are collected continuously. In the same monthly email as the educational videos, all participants will receive a request to report any falls during the past month by answering a short web-based questionnaire. In the absence of a completed questionnaire, one reminder will be sent after 1 week. All data retrieved from questionnaires, as well as application data, will be coded and reported on a group level.

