### Outcomes

#### Primary outcome

The primary and secondary outcomes, and time points of distribution are presented in table 2. The primary outcome measure will be the rate of falls (fall per person/year) during the 12 months of the intervention. To register falls, a link to a self-report online questionnaire will be sent monthly by email. To be able to report correctly the coming month, participants are asked to make notes of falls in a calendar, preferably the day the fall has occurred. They will be provided with a printable calendar in the email sent out after allocation, but they can also use their own. If a fall is reported, additional questions will be asked about the cause of the fall, potential injuries sustained, need for medical attention and hospitalisation. The number of persons falling during 12 months will be analysed based on the same data as a secondary outcome.

**Table 2 T2:** List of primary and secondary outcome measures

Outcome measures	BA	C	M	3 months	6 months	9 months	12 months
Fall rate† (fall per person/year)			X				
Number of fallers‡ (n)			X				
Number of falls during exercise with Safe Step§ (n)			X				
Fall-related injuries§ (yes/no, need of medical attention, type of injury)			X				
Hospitalisation due to falls§ (yes/no and number of days)			X				
Reach§ (self-reported sociodemographic parameters such as age, sex, years of education, use of smartphone and tablet, number of cohabitants and self-reported health and diagnosis)	X						
Self-administered 30 s chair stand test¶	X			X	X	X	X
The Borg Scale of Perceived Exertion during 30 s chair stand test** (numeric scale, score 6–20)	X			X	X	X	X
Self-rated balance**, ‘How do you perceive your balance?’ (5-level ordinal scale)	X			X	X	X	X
Self-rated leg strength**, ‘How do you perceive your leg muscle strength?’ (5-level ordinal scale)	X			X	X	X	X
Fear of falling¶ (Falls Efficacy Scale-International)	X			X	X	X	X
Health-related quality of life¶ (EQ-5D-5L)	X			X	X	X	X
Experienced positive effects of the exercise intervention§ (nominal scale, optional text field)	X*			X*	X*	X*	X*
Experienced negative effects of the exercise intervention§ (nominal scale, optional text field)	X*			X*	X*	X*	X*
Exercise adherence throughout the intervention reported through an integrated exercise diary in the Safe Step application§,¶		X*					
Exercise adherence, self-reported min/week§				X*	X*	X*	X*
Use and perceived usefulness of educational videos** (4-level ordinal scale)				X	X	X	X

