At the end of the 12-month intervention, the participants in both groups will be asked if they have started to do any other exercise activities or programmes during the intervention period. In addition, self-rated improvements in balance and leg strength over the whole course of the intervention will be measured through single-item questions. Both groups will also be asked to report if they have had any extra cost related to the intervention during the intervention period (eg, for internet access or equipment) to inform the cost-effectiveness analysis. Drop-outs and withdrawals from the study will be registered throughout the 12-month intervention. Withdrawals will be defined as those who have formally discontinued the study by filling in the withdraw questionnaire. Participants that consistently discontinue to answer the questionnaires will be defined as drop-outs.

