### Data storing and management

Participants will be assigned a pseudonymised identifying code when registering for the study. Email addresses will be collected at registration, but no names or social security numbers. Data from the online questionnaires will be directly entered into LimeSurvey software, integrated with a data collection platform, developed and hosted by ITS at Umeå University. Through LimeSurvey, several data quality features have been implemented, for example, obligatory fields and range checks.

The identity of the participants will be separated from research data entries, that is, questionnaire response and mobile-based exercise diary entries, by storing the identity in a separate database. Access to sensitive information requires a separate set of credentials. ITS at Umeå University provides all web applications, services and storage for the study. This is provided in accordance with research regulations and the General Data Protection Regulation (GDPR). Data entries will be monitored by one of the researchers throughout the study.

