### Planned statistical analyses

Analyses will be performed according to the intention-to-treat principle. Thus, all available data for each randomised participant will be analysed according to original allocation and regardless of level of participation. The primary outcome, that is, the number of falls per person year, will be analysed using negative binomial regression to account for an expected overdispersion with respect to Poisson distribution.^46^ The fall rate ratio of the two groups will be estimated with a 95% CI and presented with a p value while adjusting for the prognostic baseline covariates of age and sex for the purpose of increasing precision in estimates and statistical power. In addition, unadjusted results will be presented in accordance with recommendations from the CONSORT 2010 statement.^33^

For secondary outcomes on ordinal variables measured quarterly, analysis will be performed using cumulative link mixed models with logit link function and group, time point and group*timepoint interaction as fixed factors and participant as a random factor. In continuously scored secondary variables measured quarterly, general mixed linear models will be used to assess the group difference. Logistic regression models will be used to compare groups on dichotomous outcome measures.

Effects on falls, attrition and self-reported effects on balance and strength will be studied in subgroup analyses in relation to sex, different age groups, reported health status, physical activity and use of smartphones and tablets. Further subgroup analysis will examine exercise adherence in the exercise group as well as the dose–response relationships (min/week). Descriptive statistics will be provided to reveal the sociodemographic distribution in the sample in comparison to the population and geographical distribution in urban and rural areas.

Multiple imputation will be performed on variables containing data considered to be missing at random if proportions of missing data does not exceed 40%, as suggested in literature.^47^ In addition, analysis on original unimputed data will be presented as supplement. All statistical tests will be two sided with a significance level of 0.05.

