### Economic evaluation

Results will be presented as incremental cost-effectiveness ratio after 12 months, that is, the ratio of the difference in costs and the difference in health effects between the intervention group versus the control group. Data on health effects will be based on the primary outcome falls averted and the secondary outcome health-related quality of life assessed by the EQ-5D-5L. The data on health-related quality of life will be used to calculate quality-adjusted life years. Health and social care costs will be estimated by self-reported data on monthly falls and their consequences in combination with previously published data on the specific cost for the most frequent injuries. Resource use will include intervention costs, healthcare costs and community service costs.

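### The protocol has no planned way to learn of deaths: its drop-out definition absorbs them, so fatal falls may be missed and deaths by arm cannot be reported reliably

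*Protocol article*

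**What the plan says.** The relevant statements are spread over several sections of the protocol article.

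- **Secondary outcomes (last paragraph).** Leaving the study takes one of two forms. On the first: "Withdrawals will be defined as those who have formally discontinued the study by filling in the withdraw questionnaire". On the second: "Participants that consistently discontinue to answer the questionnaires will be defined as drop-outs".
- **Data collection.** Everything is self-reported through emailed links. For the monthly fall report: "In the absence of a completed questionnaire, one reminder will be sent after 1 week". The quarterly questionnaires get two reminders, and the second asks whether the participant wants to withdraw. No telephone call, proxy or contact person is described.
- **Primary outcome.** Details of a fall depend on the participant reporting it: "If a fall is reported, additional questions will be asked about the cause of the fall, potential injuries sustained, need for medical attention and hospitalisation". Under Secondary outcomes, the check on falls during Safe Step exercise is triggered by the same monthly answer.
- **Data storing and management.** "Email addresses will be collected at registration, but no names or social security numbers".
- **Planned statistical analyses and Table 2.** Falls are analysed as a rate per person-year, attrition by logistic regression, and EQ-5D-5L by a linear mixed model. On missing data: "Multiple imputation will be performed on variables containing data considered to be missing at random if proportions of missing data does not exceed 40"%. Unimputed results are shown as a supplement.
- **Economic evaluation.** "The data on health-related quality of life will be used to calculate quality-adjusted life years".

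Death is not mentioned as an outcome, an adverse event, a reason for leaving or a censoring event.

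**The concern.** The trial enrols people aged 70 or over who have fallen or noticed worse balance, and asks half of them to do unsupervised exercise for a year. Some deaths are to be expected. As the data flow is described, a death looks exactly like silence, and silence is a drop-out by definition.

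Four things are at stake:

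1. **Falls and safety data.** A fall that kills or incapacitates before the next monthly form has no planned route into the fall count, the injury and hospitalisation items, or the monitoring of falls during exercise. These are the most serious falls.
2. **Deaths by arm.** They cannot be reported reliably.
3. **Attrition.** This outcome is compared between arms and studied in subgroups by age and health status. Those are the subgroups in which death is most likely to be counted as loss of interest.
4. **Post-death values.** Any imputation or mixed model that is applied will treat them as missing values of a living person, because nobody knows that the person died.

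A later analysis plan can settle how known deaths are handled. It cannot recover deaths that were never recorded, and without names or social security numbers the protocol leaves no stated means of linking to a register afterwards.

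**Working it through.** **Where a participant who dies ends up.** The withdraw questionnaire has to be filled in, and a person who has died cannot do that. What remains is continued non-response, which is the drop-out category. Emailed reminders are the only planned reaction to silence. The classification therefore follows from the stated definitions.

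**How large it is.** The protocol gives no mortality figure, so there is no planned figure to reproduce. Inputs from the protocol (Sample size): N = 1400 to 2000, anticipated attrition 50%, control rate 1 fall per person-year, target rate ratio 0.80. Assumptions that are not in the protocol: one-year mortality p = 0.5% to 4%, death at mid-year on average, utility 0.8.

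- Deaths = p × N.
- Share of anticipated losses = p / 0.50.
- Share of planned person-time after death = p × 0.5.
- QALYs credited per randomised participant if living values were filled in after death = p × 0.5 × 0.8.

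| p | Deaths in 1400 | Deaths in 2000 | Share of losses | Person-time after death | QALY credit |
|---|---|---|---|---|---|
| 0.5% | 7 | 10 | 1% | 0.25% | 0.002 |
| 1% | 14 | 20 | 2% | 0.5% | 0.004 |
| 2% | 28 | 40 | 4% | 1.0% | 0.008 |
| 3% | 42 | 60 | 6% | 1.5% | 0.012 |
| 4% | 56 | 80 | 8% | 2.0% | 0.016 |

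**Primary rate ratio.** Suppose time after death were wrongly kept as fall-free exposure.

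- Equal mortality, 2% in each arm: 0.80 × 0.99 / 0.99 = 0.80.
- 1% control, 3% intervention: 0.80 × (1 − 0.015) / (1 − 0.005) = 0.788 / 0.995 = 0.792.
- 3% control, 1% intervention: 0.80 × 0.995 / 0.985 = 0.808.

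The ratio moves by about 0.01 or less even with a two-point imbalance. A missed fatal fall adds at most one event per death: at 1% to 3% mortality, at most 0.01 to 0.03 falls per participant against an assumed control rate of 1 per person-year.

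**QALY difference.** With equal mortality the credit in the table cancels between arms. Each percentage point of imbalance leaves 0.01 × 0.5 × 0.8 = 0.004. The standard error from chance imbalance alone at 700 per arm is 0.4 × √(2p(1 − p)/700) = 0.0021, 0.0030 and 0.0036 at p = 1%, 2% and 3%. With an assumed QALY standard deviation of 0.15 to 0.20, ordinary sampling error is SD × √(2/700) = 0.008 to 0.011. Combining the two in quadrature at p = 3% raises it by about 5% to 10%.

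**The case against.** The strongest case on the other side has five parts.

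- **Nothing is stated to be carried on after death.** A reader might infer that falls and quality of life are continued or imputed for people who have died. The document does not say so. A rate per person-year on the available data can stop at the last report. Imputation is conditional on data being judged missing at random with at most 40% missing, and with 50% attrition anticipated, 12-month variables may exceed that limit and not be imputed at all. This stands. What remains is conditional: where imputation or a mixed model is used, an unrecognised death is handled as a missing value of a living person.
- **Handling of known deaths belongs to an analysis plan.** Utility 0 after death and the end of exposure at death are ordinary content of a statistical or health-economic analysis plan that is not shown. This also stands, so their absence is not the fault. The fault is in data capture and in the drop-out definition, which the protocol itself fixes.
- **Deaths are not strictly invisible.** A project email account is open throughout (Interventions), and a relative could write to it or answer the withdrawal question. That is true, but no procedure provides for it. Falls reported before a death also stay in the data.
- **Being too ill to answer is not death.** A living person lost to follow-up is properly a drop-out. This stands, and the point does not rest on that group being misclassified.
- **The design is deliberate.** Minimal identifiers and high attrition are accepted openly. That is a reason not to press for more personal data, but it does not prevent a proxy answer on forms already in use.

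**Conclusion.** The point holds as a gap in ascertainment. The stated definitions, data source and identifiers give no planned way to learn of a death, and they place a participant who dies among the drop-outs. Falls that kill or incapacitate before the next monthly report may be missed, deaths by arm cannot be reported reliably, and attrition mixes death with loss of interest.

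The size is modest. Under assumed one-year mortality of 1% to 3%, deaths are 14 to 42 of 1400 and 2% to 6% of anticipated losses, and the primary rate ratio moves by about 0.01 or less even at 1% versus 3%. One might conclude that the QALY comparison is computed as if everyone lived through the year; the Economic evaluation section does not say that. The 0.004 to 0.012 QALY per participant arises only if living values are filled in after death, and it cancels if mortality is equal. Mortality, mid-year timing, utility and the QALY standard deviation are all assumptions. The case for a change rests mainly on safety reporting and on the meaning of the attrition outcome, with little threat to the primary result.

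**What to change.** 1. Add to the existing reminder emails and the withdraw questionnaire an answer for someone replying on the participant's behalf: the participant has died, the date, and whether a fall was involved.
2. Under Secondary outcomes, count known deaths separately from withdrawals and drop-outs, and report them by arm.
3. In the analysis text, end fall exposure and imputation at a known date of death, and set utility to 0 from then on.
4. State as a limitation that ascertainment of deaths and fatal falls is incomplete.

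The cost is form wording and a few sentences in the plan. The downside is partial capture: it depends on someone reading the participant's email, and it could differ between arms if engagement differs, so counts by arm need that caveat. A contact person's email address collected at registration would catch more, but it means holding a third party's data and adds an enrolment step. It is optional and would need ethics and data-protection review.

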### Data storing and management

Participants will be assigned a pseudonymised identifying code when registering for the study. Email addresses will be collected at registration, but no names or social security numbers. Data from the online questionnaires will be directly entered into LimeSurvey software, integrated with a data collection platform, developed and hosted by ITS at Umeå University. Through LimeSurvey, several data quality features have been implemented, for example, obligatory fields and range checks.

The identity of the participants will be separated from research data entries, that is, questionnaire response and mobile-based exercise diary entries, by storing the identity in a separate database. Access to sensitive information requires a separate set of credentials. ITS at Umeå University provides all web applications, services and storage for the study. This is provided in accordance with research regulations and the General Data Protection Regulation (GDPR). Data entries will be monitored by one of the researchers throughout the study.

### Sample size

The sample size calculation for the primary outcome (fall rate over the 12-month intervention period) is based on the review of Sherrington *et al*^45^ by calculating for a fall rate of 1 fall/person year. In addition, a measure of over dispersion of 1.2 is used.^21^ Thus, we require 420 participants in each group to have an 80% power to detect a 20% reduction in fall rate at a 5% level of significance. We estimate that at least 1400 participants are needed based on a calculated attrition rate of 50% and a contribution of data from drop-outs. Due to uncertain drop-out rate, we will include up to 2000 participants.

### Planned statistical analyses

Analyses will be performed according to the intention-to-treat principle. Thus, all available data for each randomised participant will be analysed according to original allocation and regardless of level of participation. The primary outcome, that is, the number of falls per person year, will be analysed using negative binomial regression to account for an expected overdispersion with respect to Poisson distribution.^46^ The fall rate ratio of the two groups will be estimated with a 95% CI and presented with a p value while adjusting for the prognostic baseline covariates of age and sex for the purpose of increasing precision in estimates and statistical power. In addition, unadjusted results will be presented in accordance with recommendations from the CONSORT 2010 statement.^33^

For secondary outcomes on ordinal variables measured quarterly, analysis will be performed using cumulative link mixed models with logit link function and group, time point and group*timepoint interaction as fixed factors and participant as a random factor. In continuously scored secondary variables measured quarterly, general mixed linear models will be used to assess the group difference. Logistic regression models will be used to compare groups on dichotomous outcome measures.

Effects on falls, attrition and self-reported effects on balance and strength will be studied in subgroup analyses in relation to sex, different age groups, reported health status, physical activity and use of smartphones and tablets. Further subgroup analysis will examine exercise adherence in the exercise group as well as the dose–response relationships (min/week). Descriptive statistics will be provided to reveal the sociodemographic distribution in the sample in comparison to the population and geographical distribution in urban and rural areas.

Multiple imputation will be performed on variables containing data considered to be missing at random if proportions of missing data does not exceed 40%, as suggested in literature.^47^ In addition, analysis on original unimputed data will be presented as supplement. All statistical tests will be two sided with a significance level of 0.05.

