### Randomisation and blinding

After completed baseline questionnaire, the participants will be randomised in a 1:1 ratio using permuted block randomisation with randomly varied block sizes. A statistician not involved in the study will generate the allocation list using the randomizeR R-package before enrolment.^36^ A computer programme developed in FLOW, Microsoft Office 365-software, will randomise participants according to the allocation list.

After randomisation, the FLOW programme will automatically send emails with follow-up questionnaires as well as the monthly fall reports and educational videos. In order to include participants, monitor data collection and answer emails regarding technical issues, two members of the research group will be able to see the participant’s email addresses and group allocation in the FLOW system and database. However, no personal contact will occur between researchers and participants regarding the results of their outcome assessments.

Analyses of the outcomes regarding falls and physical function will be made by a researcher blinded to group allocation. Participants will not be blinded due to the nature of the intervention.

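### The stated model for the ordinal quarterly outcomes does not use the pre-randomisation baseline efficiently; a common baseline mean or baseline adjustment would gain precision at no cost

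*Protocol article*

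**What the plan says.** The section Planned statistical analyses gives the model for one class of outcomes in full: "For secondary outcomes on ordinal variables measured quarterly, analysis will be performed using cumulative link mixed models with logit link function", with "group, time point and group*timepoint interaction as fixed factors and participant as a random factor". It names no baseline covariate and no constraint on the baseline means, and does not say whether baseline is one of the time points.

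Table 2 marks four outcomes for this model. Self-rated balance, self-rated leg strength and Borg exertion during the chair stand test are collected at baseline and at 3, 6, 9 and 12 months. Use and usefulness of the educational videos has no baseline measurement, so this point does not concern it. The schedule is confirmed under Data collection: "At baseline and 3, 6, 9 and 12 months, respectively, from the participant’s inclusion in the study". Under Randomisation and blinding, baseline comes first: "After completed baseline questionnaire, the participants will be randomised in a 1:1 ratio".

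For continuous outcomes such as chair stand count, FES-I and EQ-5D-5L, the article says only this: "In continuously scored secondary variables measured quarterly, general mixed linear models will be used to assess the group difference". It states no fixed effects, covariance structure or baseline handling for them.

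**The concern.** Baseline is recorded before allocation, so any difference between the arms at baseline is chance. A model with a group main effect, time and their interaction, with baseline among the time points, spends a parameter on that chance difference. Each treatment effect then becomes a difference in change from baseline. If baseline is not among the time points, the outcome's own baseline value is not used at all. Either way, information already collected is used less well than it could be.

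Self-reported balance and strength are among the named secondary aims, and heavy attrition is expected. The article itself values covariate adjustment: the fall-rate model is fitted while "adjusting for the prognostic baseline covariates of age and sex for the purpose of increasing precision in estimates and statistical power". For an outcome measured repeatedly, its own baseline value is usually the strongest covariate available, so using it would follow the same reasoning.

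**Working it through.** **Inputs.** From the article: visits at 0, 3, 6, 9 and 12 months, 1:1 allocation after baseline, and 50% attrition (Sample size: "We estimate that at least 1400 participants are needed based on a calculated attrition rate of 50% and a contribution of data from drop-outs"). Assumed, because the article gives neither: a common standard deviation σ, and a baseline-to-follow-up correlation ρ of 0.5, 0.6 or 0.7. With n participants per arm, variances below are in units of σ²/n. The article gives no precision or power figure for any quarterly outcome, so there is none to reproduce. Its 420 per group is for the fall rate only.

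**Step 1: complete data, baseline as a time level.** The 12-month interaction is a difference in change scores:
- baseline means free: 2 × 2(1−ρ) = 4(1−ρ)
- common baseline mean (equivalent to baseline adjustment): 2(1−ρ²)
- ratio, common to free: (1+ρ)/2

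| ρ | free | common | common/free | variance reduction |
|---|---|---|---|---|
| 0.5 | 2.00 | 1.50 | 0.75 | 25% |
| 0.6 | 1.60 | 1.28 | 0.80 | 20% |
| 0.7 | 1.20 | 1.02 | 0.85 | 15% |

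**Step 2: the attrition the article expects.** Exact generalised least squares, five visits, equal correlation ρ between all visits, and monotone drop-out rising linearly to 50% at 12 months:

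| ρ | free/common variance | reduction, 1 − 1/ratio | standard-error ratio |
|---|---|---|---|
| 0.5 | 1.180 | 15% | 1.09 |
| 0.6 | 1.137 | 12% | 1.07 |
| 0.7 | 1.098 | 9% | 1.05 |

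Drop-out makes the relative gain smaller. The gap between the two variances is 4(1−ρ) − 2(1−ρ²) = 2(1−ρ)², and it does not change with later drop-out because every randomised participant has a baseline. Both variances grow, so the same gap is a smaller share.

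**Step 3: the other reading, baseline not in the model.** With complete data the variance is 2 against 2(1−ρ²), a ratio of 1/(1−ρ²): 1.33, 1.56 and 1.96 for ρ = 0.5, 0.6 and 0.7. With 50% drop-out the ratios are 1.23, 1.38 and 1.65. The loss is at least as large as under the first reading.

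**Step 4: does the linear approximation carry over to the ordinal model?** Cumulative link mixed models with a random intercept were fitted to simulated five-level data (1400 participants, one data set per setting). At latent correlations of 0.5, 0.6 and 0.7, the free/common variance ratios were 1.34, 1.27 and 1.21 with complete data, and 1.18, 1.15 and 1.12 with 50% drop-out. These are close to the linear results.

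**Step 5: what causes the loss?** Step 2 was repeated with correlation decaying over time and the same baseline-to-12-month correlation. The ratios were 1.203, 1.155 and 1.112. The loss comes from the free baseline means, not from the single participant random effect.

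**The case against.** The strongest reply is that nothing here is wrong. Group, time and their interaction with a participant random effect is a standard specification, and the interaction is a legitimate effect estimate under randomisation. If baseline is a time level, its information enters the model as a response and is not thrown away. All of this stands: the point is about efficiency, not bias.

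The second reply concerns scope. A reader might infer that every quarterly secondary outcome is affected. The article does not support that. The stated terms bind only the ordinal outcomes. The linear models are not described, and this is a condensed article whose analysis plan may settle them. For chair stand, FES-I and EQ-5D-5L there is no stated defect, only a reason to use the same baseline handling.

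The third reply concerns size. A reader might take 15 to 25% as the loss in this trial. That range needs assumed correlations of 0.5 to 0.7 and no missing data. It is also a variance figure; on the standard-error scale the effect is smaller.

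A reader might also blame the participant-only random effect. Step 5 shows that it does not cause the loss. Whether equal correlation between all visits is adequate is a separate question about standard errors, and the article states no covariance for the continuous outcomes that could be called an error.

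These replies limit the point but do not remove it. The ordinal model is a stated choice rather than an omitted detail, and both readings of it lose precision at each correlation tried.

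**Conclusion.** The point holds for three ordinal outcomes: self-rated balance, self-rated leg strength and Borg exertion. With baseline as a time level, a common baseline mean would lower the variance of the 12-month effect by about 15 to 25% with complete data and about 9 to 15% with linear drop-out to 50%. The latter corresponds to standard errors about 5 to 9% larger than necessary under the stated model. If baseline is left out of the model altogether, the loss is equal or larger.

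These sizes rest on assumed correlations of 0.5 to 0.7 and a linear-model approximation that the ordinal simulations support. The direction does not depend on the value within that range. Estimates under the stated model remain valid, and the fall-rate analysis and the sample size are not touched. This is a free improvement to secondary analyses, not the correction of an error.

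**What to change.** State how baseline enters the cumulative link mixed model, in one of two ways:
- a common baseline mean: time plus group-by-follow-up-time terms, with no group main effect; or
- follow-up visits only as responses, with the participant's baseline value as covariate.

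Choose one before analysis, since the two give odds ratios on different conditional scales, and read the 12-month group contrast from it. Use the same baseline handling in the linear mixed models for chair stand, FES-I and EQ-5D-5L, if the full analysis plan does not already do so. The cost is a sentence or two of text, with no new data and no added burden on participants.
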